### Blinding and randomization

The trial participants, care providers, study investigators, outcome assessors, and data analysts will remain blinded throughout the trial period of 12 months. Treatment allocations will not be disclosed to the enrolled participants or study personnel until the conclusion of the study or in case of emergency. Only the study pharmacist, who is not involved in field or laboratory studies, will be privy to the treatment allocations in order to prepare the treatment packages accordingly. Block randomization using a 1:1 randomization ratio, stratification by helminth-infection status (infected versus uninfected), and variable block sizes of 4 and 6, respectively, will be used to randomize subjects into either the anthelmintic or placebo group. The randomization list will be generated according to OUCRU standard operating procedures. Briefly, a research biostatistician will establish a statistical code to generate the randomization list and transfer it to the study pharmacist. The study pharmacist will change the random seed, i.e., the initialization of the random number generator, in the statistical code in order to blind the research biostatistician and then run the code to prepare the final randomization list for treatment preparation. The randomization list will be password-protected and stored on a secure server to which only the study pharmacist has access. Randomization numbers, which correspond to a study ID number and a sachet of study medication, will be assigned to each enrolled participant in the clinical trial in a strict numerical sequence with individual school identifiers. Randomization numbers will be recorded on each participant’s CRF and used to identify the participant’s corresponding blinded treatment package. A total of four masked sachets containing either anthelmintic or placebo treatment will be prepared for each enrolled participant throughout the clinical trial. All participants will receive albendazole treatment at the conclusion of the study (month 12).

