
### Statistical analysis

The main analysis population includes all randomized participants, and the analysis will be conducted according to the randomized treatment arm following the intention-to-treat principle. Subgroup analyses according to helminth infection status at enrollment (infected versus uninfected) will also be performed for all endpoints.

The primary endpoint, the number of diarrheal episodes per subject, will be compared between the two study arms based on mixed-effects Poisson regression models, with treatment as the main covariate and adjustment for helminth infection status at enrollment (infected versus uninfected). To account for subjects lost to follow-up, the subject’s (log-transformed) follow-up duration will be included as an offset in the Poisson regression model. Moreover, to account for potential heterogeneity (i.e., larger between-participant variability than expected by the Poisson regression model), the participant variable will be included as a random effect in the model. If necessary, a random effect of family or household will also be included to account for non-independence of siblings or other co-inhabitants of a household. In a second step, the effect of the following covariates on diarrheal incidence will be explored: age, sex, body mass index, and household characteristics (e.g., type of water supply). A random effect of individual will be included to account for non-independence of repeated diarrheal episodes for a given individual. Additionally, the effect of helminth infection and helminth infection intensity, as determined from longitudinal stool samples, on diarrheal incidence will be investigated.

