For the secondary endpoints, the proportion of participants with STH and enteric viral and bacterial infections, as well as the infection intensities at each time point, will be summarized and visualized as line-plots over time. Formal comparisons between the treatment arms will be based on logistic mixed-effects models for proportions and linear mixed-effects models for (log-transformed) intensities using the same covariates and random effects as for the primary endpoint. The baseline measurements will be included in the analysis, but modeled as not depending on treatment arm. For the main comparison between treatment arms, only stool samples from scheduled visits will be included, as stool samples collected 2 weeks after diarrheal episodes may be unequally distributed between treatment arms. However, these additional stool samples will be included in the exploratory analyses. The effect of additional household and environmental factors present at baseline on helminth, viral, and bacterial infections will also be investigated using the same statistical modeling approach outlined above.

The taxonomic composition of the gut microbiota will be analyzed before and after helminth infection, anthelmintic treatment, and diarrhea and will be compared with individual baseline levels, between the two treatment arms, and between helminth-infected and helminth-uninfected individuals. The mothur pipeline [37] will be used to detect microbial composition and diversity between and within samples based upon the proportion of OTUs in each sample and to apply appropriate corrections for any differences driven by rare taxonomic groups of microbes. Tests, such as the LDA Effect Size (LEfSe) algorithm [38], will be used to identify significant differences in bacterial taxa between the different groups of interest.

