Cytokine levels and antibody profiles in response to parasite-specific antigens will be analyzed from longitudinally collected blood samples. Cytokine and antibody data will be log-transformed for all analyses, and linear mixed-effects modeling for analysis will be conducted as outline above. Additionally, changes in height-for-age, weight-for-age, and weight-for-height *z* scores between baseline and 12 months will be compared between the two treatment arms based on linear regression with adjustment for the baseline *z* score. Random effects to account for non-independence of siblings or other co-inhabitants from the same household will be included if necessary. Additionally, the overall number of participants with at least one adverse event (AE) or serious adverse event (SAE), respectively, will be compared between the two study arms using Fisher’s exact test. Descriptive tables will be used to summarize the frequency of all recorded AEs and SAEs by arm.

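### The z-score regression and the pooled AE/SAE test leave out the stratification factor that the other models include; if helminth status is prognostic, both are slightly conservative

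*Protocol article*

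**What the plan says.** The protocol article's Blinding and randomization section specifies a 1:1 allocation with "stratification by helminth-infection status (infected versus uninfected), and variable block sizes of 4 and 6". In Statistical analysis, the primary Poisson model has treatment and helminth status at enrollment as covariates. The models for prevalence and intensity of infection are fitted "using the same covariates and random effects as for the primary endpoint", so they carry the stratum too.

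Two comparisons later in that section are described differently:

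- Changes in height-for-age, weight-for-age and weight-for-height z scores "will be compared between the two treatment arms based on linear regression with adjustment for the baseline" z score. A household random effect is foreseen if needed. Helminth status is not named.
- The numbers of participants with at least one AE, and with at least one SAE, "will be compared between the two study arms using Fisher’s exact test". No stratification is mentioned.

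The section also states: "Subgroup analyses according to helminth infection status at enrollment (infected versus uninfected) will also be performed for all endpoints".

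**The concern.** Blocking within helminth stratum forces the arms to be nearly equal on helminth status, so the treatment difference is more precise than a simple two-arm comparison assumes. An analysis without the stratum leaves any between-stratum variation in the error term. The reported standard error is then too large and the p value too high. The plan handles this for the primary endpoint and the infection endpoints, but not for growth or adverse events.

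The trial looks for unintended effects of treatment, so a test that runs below its nominal level leans towards finding no difference. The Background section says that heavy helminth burdens can lead to growth stunting and malnutrition, so a link between the stratum and z-score change is plausible. It may be weak, because the Study area section expects mostly light infections. The planned subgroup analyses will show each stratum separately, but they do not change the pooled comparison.

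**Working it through.** The plan gives no power or error rate for these two comparisons, so there is no stated figure to reproduce.

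**Inputs from the protocol article.** There are 350 infected and 350 uninfected children, randomized 1:1, so 350 / 2 = 175 per arm per stratum and 350 per arm. The two-sided 5% level is taken from the sample-size section.

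**Assumed inputs.** The article gives neither the stratum difference in z-score change nor the AE risks, so ranges are used.

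**z scores.** Let d be the difference between strata in 12-month change, in residual SD units, after adjustment for baseline z score. With two equal strata, omitting the stratum multiplies the residual variance by 1 + d²/4. The true standard error does not change, because the arms are balanced within strata. Therefore:

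- reported SE / true SE = √(1 + d²/4)
- true type I error = 2 × [1 − Φ(1.96 × √(1 + d²/4))]
- power = Φ(2.80 − 1.96 × √(1 + d²/4)), for an effect that the adjusted model detects with 80% power

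| d | SE ratio | Type I error | Power |
|---|---|---|---|
| 0 | 1.000 | 5.0% | 80.0% |
| 0.2 | 1.005 | 4.9% | 79.7% |
| 0.3 | 1.011 | 4.75% | 79.4% |
| 0.5 | 1.031 | 4.3% | 78.3% |
| 1.0 | 1.118 | 2.8% | 72.9% |

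For d = 0.3, 1 + 0.09/4 = 1.0225, whose root is 1.011. For d = 0.5, 1 + 0.25/4 = 1.0625, whose root is 1.031. The power lost is 80.0 − 79.4 = 0.6 points and 80.0 − 78.3 = 1.7 points.

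**AEs.** Going from Fisher's test to a stratified Mantel-Haenszel test without continuity correction changes two things: exactness and stratification. An unstratified Pearson test placed between them separates the two. The simulation used 10,000 runs per scenario, 175 per arm per stratum and a common odds ratio of 2. Risks are for uninfected/infected children on placebo.

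| AE risks | Fisher | Pearson | Stratified MH | Discreteness (Pearson − Fisher) | Stratum (MH − Pearson) |
|---|---|---|---|---|---|
| 2%/2% | 26.0% | 32.0% | 32.0% | 6.0 | 0.0 |
| 2%/6% | 47.5% | 54.5% | 55.1% | 6.9 | 0.7 |
| 5%/5% | 60.0% | 65.6% | 65.6% | 5.6 | 0.0 |
| 5%/10% | 75.0% | 78.6% | 78.9% | 3.6 | 0.3 |
| 5%/15% | 83.3% | 86.0% | 86.7% | 2.8 | 0.7 |
| 10%/30% | 95.9% | 96.6% | 97.2% | 0.7 | 0.5 |

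(Differences are taken before rounding.)

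With no treatment effect, at risks of 5%/10%, the type I error is 3.3% for Fisher, 4.8% for Pearson and 4.9% for stratified Mantel-Haenszel. A continuity-corrected stratified Mantel-Haenszel test has the same power as Fisher at 5%/10% (75.0% for both), so stratifying while keeping the conservatism gains nothing visible there. In a separate run of 20,000, a wide assumed gap of 5%/25% raised the stratum's share to 92.9 − 91.4 = 1.5 points.

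**The case against.** The strongest reply is that little is at stake. These are secondary endpoints with no claimed power, the sample size is unaffected, and the error is only ever conservative. No passage quantifies a stratum difference in growth, and adjustment for baseline z score may already absorb part of it. The article is condensed, and it does not say that baseline z score is the only covariate. The stratum-specific results will be reported anyway.

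Most of that stands, and it limits the size of the point. The point survives because the article does spell out this model, down to an optional household random effect, and omits a factor that it names for the primary model.

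A reader might infer three stronger things, which the documents do not support:

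- **That ignoring the stratum explains the weakness of the AE test.** At equal risks in both strata the gap between Fisher and stratified Mantel-Haenszel is still 5.6 to 6.0 points, and none of it can come from the stratum.
- **That Fisher's test brings nothing in return.** It guarantees type I error control with sparse counts. Sparse counts are likely, since the Reporting of serious adverse events section records only grade 3 to 5 AEs and SAEs.
- **That the AE/SAE comparison is the trial's only formal look at harm.** The primary hypothesis is itself one of harm (more diarrhea under albendazole), and its model adjusts for helminth status. The Data monitoring section adds p-value guidance for excess diarrhea and for anemia.

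**Conclusion.** The point holds as a minor inconsistency between the randomization and two of the planned analyses. The pooled z-score regression and the pooled AE/SAE test omit the stratification factor that the primary and infection models include.

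- **z scores:** the standard error is about 1% to 3% too large and 0.6 to 1.7 power points are lost, if the strata differ by 0.3 to 0.5 residual SD in 12-month change. That range is an assumption. With no difference the loss is zero.
- **AEs and SAEs:** the stratum's share is about 0 to 0.7 power points in most assumed scenarios. The rest of the shortfall, roughly 3 to 7 points when events are uncommon, is Fisher's discreteness. Whether to accept that for guaranteed error control is a matter of preference, not an error in the plan.

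Neither comparison is invalid, and the primary analysis is not affected.

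**What to change.** In the Statistical analysis section, add helminth infection status at enrollment to the z-score regression: change ~ arm + baseline z score + helminth status. This costs one phrase and one degree of freedom per model. It needs no new data, since the factor is known for every randomized child.

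Optionally, for consistency, report a helminth-stratified Mantel-Haenszel estimate with a 95% CI for AEs and SAEs beside Fisher's test. If SAEs are very few, that estimate would need an exact or mid-p form. Fisher's test and the descriptive tables can stay as they are.

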### Reporting of serious adverse events

All grade three to grade five AEs and SAEs will be recorded on the participant’s CRF. AEs are graded according to their severity from 0 to 5 according to the Common Terminology Criteria for Adverse Events from National Cancer Institute [39]. A study physician will use clinical judgment to assess whether the AE/SAE is drug and/or study-related, or if it is due to the natural history of the underlying condition or disease. If a participant experiences a SAE, the study physician will inform the principal investigator and complete the specific documentations and the CRF. All SAEs will be reported to the Institutional Review Boards (IRBs) of reference, sponsors, and the Data and Safety Monitoring Board for this study.

### Data monitoring

The study will be overseen by an independent Data and Safety Monitoring Board (DSMB), who will review unblinded study data at bi-annual safety interim analyses, once before the initiation of the study and once at the 6-month time point, and can recommend stopping or modification of the trial in case accruing evidence suggests that continuing the study would be unethical. The constituents of the DSMB will have no role in the planning, conduct, or implementation of the trial itself and will serve only as a third party internal review of data and safety. The DSMB may recommend termination or modification of the study if preliminary data indicate beyond a reasonable doubt that anthelmintic treatment increases the total incidence of diarrheal disease (primary endpoint) or if the observed diarrheal incidence in either treatment group is at least tripled compared to the other. The Haybittle-Peto boundary, requiring a *p* value <0.001 at interim analysis to consider stopping for superiority of placebo, will be used as a guidance. The DSMB may also recommend termination or modification if preliminary data clearly suggest that withholding anthelmintic treatment (i.e., the placebo group) is harmful in terms of anemia. A less conservative *p* value <0.01 in the direction of harm for either of these endpoints will be used as guidance. The DSMB recommendation should not be based purely on statistical tables and *p* values, but also requires clinical judgment.

## Discussion

The WHO plans for the regular administration of anthelmintics to 75 % of all school-aged children at risk of helminth-induced morbidity by 2020 [40]. Given the rapid expansion of single-dose mass administration of anthelmintic therapy at a global level, studies assessing the impact of anthelmintic treatments on other pathogens are needed. Recently, anthelmintic trials have begun to monitor for altered risks of malarial infections in dewormed individuals [41–43]. However, studies investigating the impact of anthelmintic treatments on pathogens other than the targeted helminths remain rare. Here, we plan to investigate whether anthelmintic treatments alter the incidence of diarrheal disease caused by viral and bacterial pathogens in school children in southern Vietnam.

Two types of single-dose anthelmintics, 400 mg albendazole and 500 mg mebendazole, are recommended by the WHO for STH control [30]. For STH, the efficacy of albendazole and mebendazole varies depending on helminth species. The cure rates after a single dose of 400 mg albendazole are around 96 % for *A. lumbricoides*, 34 % for *T. trichiura*, and 69 % for hookworms [44]. With a single dose of 500 mg mebendazole, the cure rates for infection by *A. lumbricoides*, *T. trichiura*, and hookworms are around 93 %, 40 % and 31 %, respectively. Due to the higher cure rate of albendazole for hookworm infections, which are the predominant STH infections in Cu Chi district [25], and to follow the previous medication used in school-based deworming programs in this area, 400 mg albendazole was selected to be used in this study. As part of the clinical trial, we will also collect stool samples 2 weeks after the first and third treatments, which will allow us to further investigate the efficacy of albendazole in reducing STH burdens in Cu Chi district. Irrespective of the trial outcome, the data generated from this study will generate valuable information regarding the rates of helminth acquisition, intensities of helminth infections, incidence of diarrhea, and efficacy of anthelmintic treatments in school-aged children in Cu Chi district, which can inform Vietnam health officials when designing future public health programs.

Re-infection occurs rapidly after all types of deworming. Within 3 months post treatment, approximately one third of treated individuals are re-infected with STH and more than 50 % of individuals are typically re-infected 6 months post treatment [45]. In order to decrease the chances of re-infection in the anthelmintic arm, we will administer anthelmintic and placebo treatments once every 3 months in contrast to current school-based deworming programs in Vietnam, which administer anthelmintic treatments once every 6 months. The increased frequency of anthelmintic administration poses no known health risk to the individual [46]. This study design will help to minimize the helminth burden in those individuals in the anthelmintic arm and thus increase the chances of observing any potential effect of anthelmintics on diarrheal incidence.

As it is difficult to accurately assess the burden of diarrheal disease [47], an important strength of this study is the active surveillance of diarrheal cases that will be conducted during the trial. We will monitor for incidences of diarrhea through weekly active and passive surveillance. A study nurse will call the parents/guardians of each participant weekly, asking if any incidence of diarrhea has occurred. Participants will also inform the study nurse of diarrheal cases through passive surveillance. We will also collect stool samples and information regarding diarrheal symptoms with each diarrheal episode. Most studies on diarrhea focus on children under 5 years of age, and there is currently a dearth of studies reporting on diarrhea in school-aged children [48]. This study will provide valuable information regarding the causative agents and frequency of diarrhea in this age group in Cu Chi district of Ho Chi Minh City, Vietnam.

While the primary endpoint of the study is the incidence of diarrheal disease assessed by 12 months, the sample collections in this trial will also help to disentangle potential mechanisms by which helminths may be altering the incidence of viral- and bacteria-induced diarrhea. Helminths can affect both the activation of the human immune system and the composition of the gut microbiota (e.g., [49, 50]), and these alterations may impact the colonization or invasion of enteric viral and bacterial pathogens that share the same intestinal niche. The blood and stool samples collected in this study will help to assess biological differences in immune function and gut microbial communities between infected and uninfected individuals and between treatment groups, which may elucidate potential mechanisms by which helminths interact with diarrheal pathogens in the human gut.

Ultimately, this study will provide an important first test of whether anthelmintic treatment has unintended effects on the health of school children and their subsequent risks of infections due to enteric viral and bacterial pathogens. This study is timely and much needed, as diarrhea remains a major concern for child health worldwide, as deworming programs are becoming routine in developing countries, and as growing experimental evidence suggests that anthelmintic treatments may increase host susceptibility to other infections (bacteria, viruses, or protozoa) [14–18]. We aim to investigate whether current mass administrations of anthelmintic treatments indirectly impact the disease dynamics of co-infecting pathogens by focusing on diarrheal pathogens that inhabit the same intestinal niche as STH. Our results will provide new insights into the role of co-infections in the success of treatment strategies in developing countries and will elucidate the importance of both the microbiota and macrobiota in human health. Further relevant aims of this study are to inform public health policies of potential indirect effects of mass deworming programs on other co-infecting pathogens and to inform WHO recommendations on anthelmintic dose regimens for Cu Chi district and beyond.

## Trial status

This study has started participant recruitment.

## Abbreviations

AE, adverse event; CRF, case report form; DSMB, Data and Safety Monitoring Board; ID, identification; IL, interleukin; IRB, Institutional Review Board; LEfSe, LDA Effect Size; mg, milligrams; OTUs, operational taxonomic units; OUCRU, Oxford University Clinical Research Unit; PBMCs, peripheral blood mononuclear cells; PCR, polymerase chain reaction; SAE, serious adverse event; STH, soil-transmitted helminth; WHO, World Health Organization
